### Data collection, management, and monitoring

Before the trials commence, all investigators undergo comprehensive training on the clinical trial protocol, data management, and indicator evaluation methodology. Throughout the study, investigators diligently collect and record data in the participants’ medical records. All adverse events are carefully documented in the electronic case report form (CRF).

Participants who cannot be followed up for the entire study duration are considered dropouts. Participants have the option to withdraw from the study voluntarily in cases of intolerable side effects or poor treatment efficacy. Additionally, participants can withdraw from the study at any time for any reason. The investigators have the authority to withdraw participants from the study to prioritize their safety.

Any modifications to the study protocol require prior approval from the institutional ethics committee at Dongyang People’s Hospital. Once approved, these changes must be documented in the trial registry and subsequently included in the final research data report. Significant protocol amendments will be effectively communicated to trial participants through various channels, including written notifications, verbal explanations, or informational sessions. Participants will be given opportunities to seek clarification, ask questions, or express any concerns they may have.

During the experiment, concurrent treatments such as chronic diabetes, hypertension, anxiolytics, and antidepressant drugs are accepted. After all the follow-ups, participants are asked about receiving any other interventions during the study period, and this information is reported in the study results.

To minimize data loss, all participants are provided with guidance when they sign the informed consent form and commit to attending the scheduled treatment dates. Participants receive an appointment card to attend sessions. An evaluator is responsible for notifying and monitoring the participants every week (via telephone contact, WeChat, and/or email) and accompanying them during the research.

To ensure data quality control, the data manager conducts regular and timely data monitoring. When adding a new patient to the database, their identifying data is recorded on a printed form, which is not stored on the server. On this form, the participant’s name is represented by a combination of four English letters (the initials of their Chinese name pronunciation). This form is securely stored in a locked space, accessible only to the principal investigator, and may be utilized to reveal personal data if the need arises for unblinding purposes. Access to the final dataset is restricted solely to the principal investigator and the statistician, ensuring confidentiality and maintaining the integrity of the data. The data management team will maintain ongoing communication with the investigators regarding the progress of the trial, data consistency, instances of missing data, and any violations of time windows. If needed, queries for missing data and requests for clarification of inconsistencies or discrepancies will be issued.

The study will be overseen by the Data and Safety Monitoring Board (DSMB), comprising physicians, ethicists, medical statisticians, and a clinical manager. Their role involves regular monitoring, scheduled every 3 months. The DSMB will review safety data and clinical effectiveness reports to make informed decisions on whether the clinical trial should proceed.

### Statistics analysis

A comprehensive analysis is performed to delineate the demographic and clinical characteristics of the patient population. The normality of the variables is assessed using the Shapiro–Wilk test. The evaluated variables are depicted in tabular form, displaying both absolute and relative frequency distributions. Associations are examined utilizing either Pearson’s chi-square test or Fisher’s exact test, as warranted. The statistical significance of mean differences among quantitative variables is assessed through the paired and unpaired *t*-student tests. To assess variations across different time points within a group, the analysis of variance (ANOVA) with repeated measures is employed.

Continuous data are presented as mean ± standard deviation (SD), while categorical data are represented as counts (percentages). All analyses follow a two-tailed approach, with a significance level of 0.05. The statistical software package SPSS 17 (IBM Corporation, Armonk, NY) is employed for conducting data analysis, by established procedures.

In instances of data discontinuity, missing data will be handled by the “intention-to-treat” principle for conducting inferential statistical analysis. Missing data will be addressed through a dual strategy involving the last observation carried forward (LOCF) method and multiple imputation (MI). Additionally, sensitivity analyses will be conducted to evaluate the influence of various imputation methods on the study outcomes.

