Although numerous studies have demonstrated the efficacy and safety of YAG laser vitreolysis, there remains controversy among some researchers regarding its widespread clinical use [9]. They argue that, as with any new treatment modality, moderate skepticism is warranted until further research demonstrates a favorable risk/benefit ratio. Additionally, Shah’s research found that objective improvement in patients’ vitreous floaters was 94%, while subjective improvement was only 53%, indicating a clear disconnect between objective and subjective responses that must be taken into account. On the efficacy front, the majority of current research does not rule out the placebo effect, as symptoms of vitreous opacities themselves may improve with gravity and neural adaptation. Complications of YAG laser are also worth paying attention to, such as lens damage, retinal hemorrhage, retinal vein occlusion, and postoperative high intraocular pressure [10–13]. To reduce intraoperative complications, YAG laser vitreolysis is recommended for patients with stable Weiss rings, with floaters located more than 2 mm away from the retina and more than 5 mm away from the lens [14].

To reduce intraoperative complications, current randomized controlled trials require inclusion criteria of patients with vitreous floaters lasting more than 6 months and completed posterior vitreous detachment [7, 15], which is not clinically practical. Many patients require intervention in the early stages of symptoms. There is a lack of research on the safety and efficacy of early YAG laser vitreolysis. Therefore, we undertook this clinical study to uncover that early YAG laser vitreolysis is both a safe and effective treatment option for vitreous floaters.

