### Randomization and masking

In this study, a stratified randomization method will be used to allocate participants to two groups in a 1:1 ratio, using SPSS v26.0 (SPSS Inc, Chicago, IL, USA). The randomization process incorporates minimization and involves the consideration of three study variables for group stratification: sex (male/female), age (> 50/ ≤ 50 years), and crystal state (phakic eye/pseudophakic eye). A random allocation sequence will be created in advance and sealed in sequentially numbered opaque envelopes, allowing for randomization one at a time. Group allocation will be carried out by another researcher to ensure the randomization process is unbiased. All researchers involved in the study, including outcome assessors, statisticians, and data analysts, will be blinded to group assignment, but those providing the intervention will be informed as necessary. Before the trial, researchers will undergo comprehensive training in the randomization procedure and will be made aware of their responsibilities. The successful implementation and maintenance of the randomization and blinding methods will be validated to ensure the reliability and absence of bias in the trial results.

The investigator is strongly advised to uphold the blinding to the greatest extent possible. The actual allocation should not be revealed to the patient or any other study personnel, including site personnel, monitors, or project office staff. There should also be no written or verbal disclosure of the code in any of the patient-related documents associated with the study.

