### Secondary outcome

The secondary outcomes of the study encompass the objective assessment of changes through OCT and fundus photography. The objective evaluation of vitreous floater improvement using OCT and fundus photography is categorized into five levels: worsening, no change, mild improvement, significant improvement, and complete improvement. The objective evaluation will be conducted at 3, 6, 9, and 12 months.

Other secondary outcomes include the incidence and severity of ocular and systemic adverse events, such as retinal tears, retinal hemorrhage, retinal detachment, lens damage, and other related adverse events. The incidence rates of these adverse events will be recorded immediately after each laser treatment and at 1-month post-treatment.

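### Named tests adjust for neither baseline score nor the allocation factors, and change over time is tested only within arms; this gives up precision, and the within-arm tests should be labelled descriptive

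*Protocol article*

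**What the plan says.** The Statistics analysis section of the protocol article lists its inferential tests.

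- **Quantitative outcomes:** "The statistical significance of mean differences among quantitative variables is assessed through the paired and unpaired" t-tests.
- **Repeated visits:** "To assess variations across different time points within a group, the analysis of variance (ANOVA) with repeated measures is employed".
- **Categorical outcomes:** "Associations are examined utilizing either Pearson’s chi-square test or Fisher’s exact test, as warranted".

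No covariate, stratified analysis or group-by-time term appears in that list.

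Other sections bear on the choice:

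- Randomization and masking: "The randomization process incorporates minimization and involves the consideration of three study variables for group stratification". The three are sex, age (split at 50 years) and lens status (phakic or pseudophakic).
- Inclusion criteria: entry requires a disturbance score of at least 4 on the 0–10 scale, so each participant has a baseline score.
- Primary outcome: the two measures are improvement on the 0–10 scale and mean change in NEI VFQ-25.
- Secondary outcome: the image assessment "is categorized into five levels: worsening, no change, mild improvement, significant improvement, and complete improvement", which is an ordered scale.
- Background: the authors note that "symptoms of vitreous opacities themselves may improve with gravity and neural adaptation".

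**The concern.** Three features of the design are not carried into the named analysis.

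1. **Allocation factors.** Balancing the arms on a factor that predicts outcome reduces the true variance of the difference between arms. A t-test that leaves the factor out does not see that reduction, so its standard error is too large.
2. **Baseline score.** Baseline enters, at best, by subtraction. Regression on baseline is at least as precise and usually more so.
3. **Time.** The only longitudinal method named works inside one arm. A within-arm change mixes any laser effect with adaptation and with regression to the mean from the entry threshold. The early-versus-delayed question needs a contrast between arms across visits, and none is named.

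A lesser point is that chi-square and Fisher tests discard the order of the five image grades. At stake are power in a trial of 70 patients with slow recruitment, and a clear statement of which results speak to efficacy.

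**Working it through.** **1. The plan's own figure.** Inputs from Sample size calculation: improvement 30% v 10% (difference 20), SD 25, alpha 0.05, power 0.90; two-sided per Statistics analysis.

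n per arm = 2 × (1.960 + 1.282)² × 25² / 20² = 32.8, so 33 per arm and 66 in all. With 5% loss, 66 / 0.95 = 69.5, so 70. Both stated numbers reproduce, and the calculation is an unadjusted two-sample comparison of means. With the t distribution, power at 33 per arm is 89% (90.1% by the normal approximation).

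**2. Adjusting for baseline.** Take the SD of 25 as that of a change score. Let r be the baseline-to-follow-up correlation and k the baseline SD divided by the follow-up SD. Then

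Var(ANCOVA) / Var(change) = (1 − r²) / (1 + k² − 2rk),

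which is (1 + r)/2 when k = 1. The article gives neither r nor k, so both are assumed. The entry threshold truncates baseline scores and not later ones, which makes k below 1 plausible. Example with r = 0.5 and k = 0.8: 0.75 / 0.84 = 0.893; SD = 25 × √0.893 = 23.6; power 92%.

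| k | r = 0.3 | r = 0.5 | r = 0.7 |
|---|---|---|---|
| 1.0 | SD 20.2, power 98% | SD 21.7, 96% | SD 23.0, 93% |
| 0.8 | SD 22.1, 95% | SD 23.6, 92% | SD 24.8, 90% |
| 0.6 | SD 23.8, 92% | SD 24.8, 90% | SD 24.8, 90% |

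When r = k the ratio is exactly 1 and nothing is gained: at r = k = 0.6, 0.64 / 0.64 = 1. The formula concerns absolute change. The article sizes on percentage improvement, so the table is a guide and not a forecast.

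**3. Leaving out the allocation factors.** Suppose one perfectly balanced factor explains a share R² of the outcome variance (assumed 10% or 20%). The t statistic is then too small by a factor √(1 − R²), and the true two-sided error is about 2 × [1 − Φ(1.96 / √(1 − R²))]: 3.9% at R² = 0.1 and 2.8% at R² = 0.2. Simulation of 20,000 trials at 33 per arm gives 4.0% and 2.9%. The test is conservative.

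**4. What a within-arm test shows.** Use the plan's sham figure: mean 10, SD 25, n = 33. The noncentrality is 10/25 × √33 = 2.30, against a critical t of 2.04 on 32 degrees of freedom. A paired test is significant 61% of the time. If both arms improve by 10 and the laser does nothing, exactly one arm is significant in 2 × 0.606 × 0.394 = 48% of trials. The unpaired test in the same setting rejects 5.2% of the time (simulated), as it should.

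**5. Image grade.** With assumed control grades of 10/50/20/15/5%, an assumed odds ratio of 3 and 35 per arm, simulated power is about 45% for chi-square and 70% for a rank test. Only the direction carries over to other inputs.

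**The case against.** **Baseline is already used.** A reader might infer that the plan ignores baseline. The article does not support that: its primary outcomes are an improvement and a mean change, and it sizes the trial on improvement, so baseline plausibly enters by subtraction or ratio. This stands. What is missing is baseline as a covariate.

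**Natural improvement is already controlled.** A reader might also infer that spontaneous recovery will be counted as efficacy. The trial is randomized, masked and sham-controlled, it is sized on laser against sham, and an unpaired test is named. That comparison cancels adaptation and regression to the mean up to month 3. No sentence makes a paired test or the within-group ANOVA the test of efficacy, and the 61% in step 4 is correct detection of a real change in the sham arm. This stands too. What remains is that the article does not say which test decides efficacy, so the role of the within-arm tests needs stating.

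**The gain may be small.** It depends on unstated r and k, and nothing in the article shows that sex, age or lens status predicts symptom change. This is accepted: the 93–98% in the first row of the table needs equal SDs.

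**This belongs in the SAP.** A covariate list often does, and its absence alone would be no finding. Here, though, the article names the tests, and those it names are unadjusted or confined to one arm.

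**The image grade is a separate, secondary matter.** The chi-square sentence is generic and is not tied to that outcome. It is therefore kept as a minor part of the fix.

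**Conclusion.** The point holds as one of efficiency and labelling. The unpaired comparison to month 3 is valid. Leaving out the allocation factors does not inflate type I error; it lowers it, to about 3–4% if a balanced factor explains 10–20% of variance (assumed). The stated 66 and 70 are not wrong.

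At 33 per arm, baseline adjustment moves power from 89% to roughly 90–98% for r of 0.3–0.7 and k of 0.6–1, with no gain where r equals k. The paired tests and the within-group ANOVA cannot isolate a laser effect, and no arm-by-visit comparison is named to do so across visits. The change should be made, and made before unblinding so that the adjustment cannot look data-driven.

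**What to change.** - **Primary comparison:** analyse the month-3 0–10 score, and likewise NEI VFQ-25, by ANCOVA on arm, baseline score, sex, age group and lens status. The month-3 assessment should be the one made before the delayed arm's laser.
- **All visits:** replace the within-group ANOVA with one mixed model containing arm, visit, arm-by-visit and the same covariates. After month 3 its arm contrasts compare early with delayed laser, not laser with sham.
- **Paired and other within-arm tests:** state that they are descriptive and do not decide efficacy.
- **Five-level image grade:** use a Wilcoxon rank-sum test or a proportional-odds model.

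The cost is wording in the protocol and the SAP. Baseline scores are needed for eligibility and for the change outcomes, and the three factors are needed for allocation, so no new data or patients are required and the sample size need not change.

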**Methods:**

The present study is a randomized, controlled, double-blind clinical trial. A total of 70 participants with symptomatic floaters for 1 month were prospectively recruited. These participants will be randomly assigned to two groups, with 35 individuals in each group: the early treatment group and the delayed treatment group. Participants assigned to the early treatment group will undergo YAG laser vitreolysis immediately, followed by a sham laser treatment 3 months later. On the other hand, participants assigned to the delayed treatment group will receive a sham laser treatment and then undergo YAG laser vitreolysis 3 months later. The follow-up time points will be 1, 3, 6, and 12 months from randomization. Primary outcomes will be participants’ self-reported improvement in visual disturbance on a scale of 1 to 10 and their scores on the National Eye Institute Visual Functioning Questionnaire 25 (NEI VFQ-25). Secondary outcomes will be an objective evaluation of the effectiveness of the treatment in reducing vitreous floaters through OCT and fundus photography and tracking any adverse events related to the eyes or overall health.

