### Primary outcome

The study will measure the outcomes at 3, 6, 9, and 12 months. These outcomes include the subjective improvement in floater symptoms, which is rated on a scale of 0 to 10. A score of 0 represents no symptoms, while a score of 10 indicates symptoms that significantly impact daily life. The study also measures the mean change in the National Eye Institute Visual Functioning Questionnaire-25 (NEI VFQ-25), which is a self-reported questionnaire that evaluates a patient’s visual function and its effect on their quality of life. The VFQ-25 consists of 25 items, which assess different domains of vision-related quality of life, including general vision, near and distance activities, driving, social functioning, and mental health. The minimum score for the VFQ-25 is 0, indicating the worst possible visual function and quality of life, while the maximum score is 100, representing the best possible visual function and quality of life. Higher scores on the VFQ-25 indicate better outcomes, indicating that the patient has improved visual function and quality of life. To address multiple comparisons in our study, we applied a Bonferroni correction. This correction method adapts the significance level to maintain an overall alpha level of 0.05, effectively controlling for the heightened risk of type I error associated with multiple testing.

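### LOCF can carry a delayed-arm sham-phase score past that arm's month-3 laser, and the plan pairs LOCF with MI without saying which gives the primary result

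*Protocol article*

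**What the plan says.** The Statistics analysis section of the protocol article invokes intention-to-treat as the way to deal with incomplete data: "missing data will be handled by the “intention-to-treat” principle for conducting inferential statistical analysis". It then names two imputation methods side by side: "Missing data will be addressed through a dual strategy involving the last observation carried forward (LOCF) method and multiple imputation (MI"). It adds that "sensitivity analyses will be conducted to evaluate the influence of various imputation methods on the study outcomes", but gives no reference method against which the others are to be judged.

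The abstract's Methods paragraph sets out the two treatment sequences. For one arm, "Participants assigned to the early treatment group will undergo YAG laser vitreolysis immediately, followed by a sham laser treatment 3 months later". For the other, "participants assigned to the delayed treatment group will receive a sham laser treatment and then undergo YAG laser vitreolysis 3 months later".

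The Primary outcome section says: "The study will measure the outcomes at 3, 6, 9, and 12 months". Three of those four time points fall after the delayed arm's laser. The section on data collection, management and monitoring lets patients leave for reasons tied to the outcome: "Participants have the option to withdraw from the study voluntarily in cases of intolerable side effects or poor treatment efficacy".

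**The concern.** LOCF assumes that a patient's score stays where it was at the last visit. In this design the treatment itself changes at month 3, and the change means different things in the two arms. In the early arm, any post-baseline score follows laser, so a carried value belongs to the same treatment state as the value it replaces. In the delayed arm, a score from month 1 or month 3 reflects sham. Carried to months 6, 9 and 12, it stands in for a score that should follow laser.

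If laser works better than sham, this makes the delayed arm look worse at the late time points, and so makes early treatment look better. The Methods/design section labels the trial non-inferiority. If that label governs the late comparison, an error in this direction is anti-conservative.

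The second issue is that two methods with different assumptions are named and neither is ranked first. They can give different estimates and standard errors. As written, the choice of which one to report as the main result stays open until the data are seen, for two primary measures at four time points each.

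**Working it through.** **Inputs.**
- Sample size calculation section: improvement of 30% with laser and 10% with sham, SD 25%, alpha 0.05, power 0.9, 66 patients, 5% loss, 70 enrolled.
- Statistics analysis section: two-sided tests.
- Abstract, Methods: 35 patients per arm, and the month-3 switch.

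**The plan's own figure.** By the normal approximation, n per arm = 2 × (1.960 + 1.282)² × 25² / 20² = 32.8, rounded up to 33, so 66 in total. Allowing for 5% loss, 66 / 0.95 = 69.5, rounded up to 70. Both stated figures reproduce.

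**Who is affected.** Only delayed-arm patients whose last score precedes their laser. Under either schedule in the article ("The follow-up time points will be 1, 3, 6, and 12 months from randomization" in the abstract, or months 3, 6, 9 and 12 under Primary outcome), the first efficacy assessment after the month-3 laser is at month 6. The one-month check after each laser session, in the Secondary outcome section, concerns adverse events. A patient lasered at month 3 who then attends no later visit would therefore have a sham-phase score carried forward. A patient seen at month 6 and lost afterwards carries a post-laser score and is not affected.

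**Size of the shift.** Suppose both arms truly average 30% improvement after laser, so that the true late difference is zero. Let p be the share of the delayed arm last scored before its laser. The delayed-arm mean under LOCF is (1 − p) × 30 + p × 10 = 30 − 20p, so the shift toward early treatment is 20p points.

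The standard error of the arm difference is 25 × √(2/35) = 5.98. The chance of a significant result favouring early treatment is 1 − Φ(1.96 − 20p/5.98), which is 2.5% when p = 0.

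| p | Patients of 35 | Shift (points) | Shift / SE | Chance of false finding for early |
|---|---|---|---|---|
| 5% (all planned loss before laser) | 1.75 | 1.0 | 0.17 | 3.7% |
| 10% (assumed) | 3.5 | 2.0 | 0.33 | 5.2% |
| 20% (assumed) | 7 | 4.0 | 0.67 | 9.8% |

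**Simulation.** With 40,000 simulated trials of 35 per arm, an assumed within-patient correlation of 0.5, 5% loss in the early arm and loss unrelated to outcome, the mean shift was 1.06, 1.97 and 4.06 points at delayed-arm losses of 5%, 10% and 20%. The chance of a false finding for early treatment was 3.8%, 4.9% and 9.6%, against 2.6% with no loss. This agrees with the formula.

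**The case against.** **The effect is small at the planned loss.** One point against a standard error of 5.98 will rarely change a conclusion. Even that is an upper-end figure, because it puts the whole 5% before the laser. This stands. Losses of 10% and 20% are assumptions and appear nowhere in the document.

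**The comparison the trial is sized on escapes.** The sample size rests on laser versus sham, a contrast that exists only up to month 3. This also stands: a value carried to month 3 crosses no treatment switch.

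**A sham score may suit someone who left and was never lasered.** This stands in part. The 20-point error is measured against the outcome had the laser been given, and for a never-lasered patient the frozen score may be closer to what happened. It does not cover the patient who was lasered at month 3 and then missed later visits. Even for the unlasered patient, the Background expects symptoms may ease through gravity and neural adaptation, which a flat line denies. Intention-to-treat settles who is analysed, not what value replaces a missing one.

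**Ranking methods is detail for a SAP, and sensitivity analyses are promised.** The article does more than stay silent. It fixes two methods jointly, and one of them is ill suited to the design. The promised sensitivity analyses would show a divergence but not say which result counts.

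**Stronger readings that the documents do not support.** A reader might infer that every delayed-arm patient lost after month 3 is scored 20 points too low. Only those last scored before the laser are affected, and 30% and 10% are group means. A reader might also infer that the bias always favours early treatment. That needs laser to beat sham, and withdrawal for poor efficacy is open to both arms, so low early-arm scores carried forward could offset part of the shift. Finally, the abstract's visit list omits month 9, which might suggest that the whole time point would be filled by LOCF. The Primary outcome section says month 9 is measured, and nothing says LOCF would fill it. That is a separate inconsistency in the schedule.

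**Conclusion.** The point holds in limited form. LOCF as written can place sham-phase scores in the post-laser period of the delayed arm and not of the early arm, and the plan leaves open whether LOCF or MI is primary. The resulting shift in the comparisons after month 3 is about 20 points times the share of the delayed arm last scored before its laser: at most about 1 point at the planned 5% loss. It becomes material only if sham-phase loss is well above plan, which the permitted withdrawal for poor efficacy makes plausible but does not establish.

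The size rests on three assumptions: laser beats sham as the sample size section supposes, the month-3 score is taken before the month-3 laser (the order is not stated), and the target is the outcome with the delayed laser given. The plan should be changed on this point, but the point does not undermine the trial's powered contrast.

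**What to change.** Name one primary method. Either of two would serve: a likelihood-based mixed model on all visits, or MI carried out separately by arm, using baseline, the allocation factors (sex, age group, lens status) and all observed visits. Drop LOCF, or keep it only as a labelled sensitivity analysis that does not carry values across month 3. For the main sensitivity analysis, use MI by arm with a stated shift (delta) applied to the missing values. This tests departures from the primary assumption directly, including poorer outcomes among those who left.

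The cost is wording and a little more analysis work. Sample size, visits and treatment do not change. The Trial status section reports 32 participants enrolled at 19 September 2023, with recruitment extended to December 2024.
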